### Statistical analysis

Baseline patient and procedure characteristics and perioperative outcome parameters are categorical, continuous and dichotomous variables, and will be presented accordingly. The chi-square test will be used to compare dichotomous and categorical data among patient groups. Descriptive outcomes will be reported as median with interquartile range (IQR) or mean with standard deviation (SD). According to their distribution, the Mann–Whitney *U* test will be used to evaluate intergroup variation.

Oncological outcomes will be determined using Kaplan–Meier analyses, with comparison of relevant patient groups using the log-rank test. Predictors of main outcome parameters will be determined by selecting relevant variables based on expected association with subsequent univariate analysis. Alongside the stratified comparisons as described above, multivariate analysis will be performed to determine the independent association of factors with a specific outcome parameter using logistic and Cox regression analyses. A *p* value of less than 0.05 will be considered to be statistically significant. All analyses will be performed with IBM SPSS statistics, version 23.00 (IBM Corp Amonk, NY, USA). Design of the CAT will be assessed to test reliability using generalizability theory. The outcome parameters of the CAT will be compared with clinical outcomes using univariate analysis and multivariate analysis to determine the independent association of factors with a specific outcome parameter using logistic and Cox regression analyses.

Before data is locked for analysis, the statistical analysis plan will be completed, and decisions will be made on stratification criteria, planned subgroup analysis, and how to handle baseline imbalance.

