### Outcomes

The primary outcome of the current study is safety based on the overall 90-day postoperative morbidity rate, analysed and classified according to Clavien–Dindo [20]. Secondary outcomes include (1) intraoperative complications (i.e. vascular injury, injury to other organs), (2) 90-day mortality, (3) conversion rate, (4) operative time (minutes), (5) blood loss (millilitres), (6) validated assessment of the whole procedure using a CAT, (7) grading of the resection specimen according to Benz et al. [21], (8) total lymph node count in the specimen by the pathologist, (9) number of resected tumour-positive lymph nodes, (10) resection margins, (11) completeness of mesocolic excision based on the postoperative CT imaging (as performed 1 year postoperatively in regular oncological follow-up), (12) frequency of locoregional recurrence, (13) occurrence of distant metastasis, (14) 3-year DFS, (15) 5-year OS and (16) long-term surgical morbidity such as incisional hernia and adhesion-related small bowel obstruction.

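### Specimen grade, an ordered secondary outcome, falls most naturally under an unordered chi-square test, which gives up some power for a directional effect (minor)

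*Protocol article*

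**What the plan says.** The Statistical analysis section sorts variables into three types: "perioperative outcome parameters are categorical, continuous and dichotomous variables, and will be presented accordingly". It gives one test to two of them: "The chi-square test will be used to compare dichotomous and categorical data among patient groups". A sentence on medians with IQR and means with SD follows. Then, depending on distribution, a Mann–Whitney "test will be used to evaluate intergroup variation"; the variables it covers are not listed. The regression models named are logistic and Cox. Neither an ordinal class nor a trend test nor an ordinal model appears. The significance level is a p "value of less than 0.05 will be considered to be statistically significant", without a statement of sidedness.

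The Outcomes section lists grading of the resection specimen by a cited scheme as secondary outcome 7, and completeness of mesocolic excision on the 1-year CT as outcome 11. The number of levels is given for neither. The primary outcome is "safety based on the overall 90-day postoperative morbidity rate, analysed and classified according to Clavien–Dindo". The Sample size calculation treats it as a proportion, 26% with a margin of 7 points.

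Secondary objective 4 is the effect of training and proctoring on surgical quality, compared across the control, implementation and consolidation cohorts. The analysis plan is to be completed before data lock. The decisions named for that stage are stratification criteria, subgroups and baseline imbalance.

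**The concern.** A quality grade is neither continuous nor dichotomous, so under the stated three-way sorting it lands in the categorical class and hence with chi-square. Pearson's statistic for an r × c table does not change if the grade labels are shuffled. With K grades it spreads its power over K − 1 degrees of freedom for two cohorts, or 2(K − 1) for three. The study expects something narrower: that training moves specimens towards better grades. A test that ignores the order can miss a consistent shift that the collected data would show. It can also reach significance on a scatter across grades that supports neither better nor worse surgery.

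At stake is the efficiency of a secondary comparison that bears on objective 4. The validity of the trial's main conclusion is not in question.

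**Working it through.** **The plan's own figure.** The only sample size in the article is 365 per cohort, for the primary endpoint. It is reproduced by a non-inferiority formula with control against the two later cohorts pooled (1:2):

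n = (z₀.₉₅ + z₀.₈₀)² × p(1 − p) × (1 + 1/2) / margin² = (1.645 + 0.842)² × 0.26 × 0.74 × 1.5 / 0.07² ≈ 364.1, rounded up to 365.

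The pooling is inferred from the match and is not stated in the article. This calculation uses a binary rate only, so no graded outcome enters it. The article states no power for specimen grade, so there is no figure of that kind to reproduce.

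**Inputs for the graded comparison.** From the documents: 365 per cohort and the 0.05 level. Assumed: two-sided testing, the number of grades K, their distribution, and a shift in one direction (a common odds ratio across cut-points).

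**Analytic check, two cohorts.** A 1-df ordered test with 80% power at two-sided 5% has noncentrality of about (1.960 + 0.842)² = 7.85. Put the same noncentrality into a chi-square on K − 1 df:

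| Grades K | df | Chi-square power | Loss from 80% |
|---|---|---|---|
| 3 | 2 | 70.9% | 9 points |
| 4 | 3 | 64.5% | 15 to 16 points |
| 5 | 4 | 59.5% | 20 to 21 points |

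With the ordered test at 90% power the chi-square figures are 83.5%, 78.4% and 74.0%, so the losses are 6.5, 11.6 and 16.0 points.

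**Simulation check** (365 vs 365, tie-corrected Wilcoxon; 20,000 runs per scenario for 3 and 4 grades, 6,000 for 5):

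| Assumed grades | Odds ratio | Chi-square | Wilcoxon | Loss |
|---|---|---|---|---|
| 3 (20/30/50%) | 1.3 | 36.7% | 46.0% | 9.3 |
| 3 | 1.5 | 71.7% | 80.8% | 9.1 |
| 3 | 1.8 | 96.2% | 98.2% | 2.0 |
| 4 (10/20/30/40%) | 1.3 | 33.4% | 49.0% | 15.6 |
| 4 | 1.5 | 69.6% | 84.1% | 14.5 |
| 4 | 1.8 | 96.1% | 98.9% | 2.8 |
| 5 | 1.3 to 1.5 | 32 to 69% | 51 to 86% | 17 to 23 |

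The simulation agrees with the analytic figures and shows the loss fading as power approaches 100%. With four equal grades and no shift, chi-square rejects in 5.2% and Wilcoxon in 5.1% of runs, so there is no type I error problem.

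**Where the replacement would do harm.** Take Clavien–Dindo 0 to V, assumed at 74/8/10/4/2/2% in control and 74/5/7/7/4/3% later. The overall rate stays at 26% and only severity among complicated patients moves. Chi-square then has 71% power, Wilcoxon on grades 0 to V 8%, and a linear-by-linear test 29%. The rank test is dominated by the 74% tied at grade 0, so it barely sees a change confined to the complicated patients.

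**The case against.** The strongest reply is that the assignment is inferred. The article never says that specimen grade goes to chi-square, and its Mann–Whitney sentence lists no variables, so a rank test for grades is not excluded. That stands as a limit on how firmly the point can be put. But the Mann–Whitney sentence follows the one on medians and means and turns on distribution, which points to continuous data. If it did cover grades, two tests could apply to one outcome. It also compares only two groups, while objective 4 sets out three cohorts and no three-group rank test is named.

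Second, test choice for each secondary outcome is commonly left to the analysis plan, which is pending. This is why the point is minor. It remains a point because the article does state a rule for categorical data, and test choice is not among the decisions it lists for later.

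Third, chi-square on ordered categories is a valid test, and the Background names the video-based competency tool, not specimen grade, as the instrument for assessing surgical quality. Both are correct.

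A reader might also infer that Clavien–Dindo severity is wrongly tested, with a loss of about 25 points. The documents do not support this. The primary outcome is a rate, hence binary, and none of the 16 secondary outcomes is a between-cohort comparison of complication grade. A rank test on grades 0 to V could also hide the severity change it was meant to show.

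**Conclusion.** The point holds in a limited form and is minor. On the natural reading of the Statistical analysis section, specimen grade would be compared as unordered categories, as would CT completeness if it is recorded on an ordered scale, although the expected effect is directional. The cost is roughly 9 to 20 points of power. That rests on assumptions absent from the documents: 3 to 5 grades, a shift in one direction, 365 vs 365, and an ordered test at about 80% power. It falls to 2 to 3 points in the 3- and 4-grade examples at an odds ratio of 1.8, and it can reverse for a change that is not monotone. No single figure can therefore be stated as the plan's actual loss. Type I error, the binary primary endpoint and the 365 per cohort are untouched.

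**What to change.** In the Statistical analysis section, or in the analysis plan still to be completed:

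- Limit the chi-square test to dichotomous and nominal variables.
- Compare specimen grade, and CT completeness if it is graded in order, by Mann–Whitney for two cohorts or Kruskal–Wallis for three.
- For adjusted analyses of these outcomes, use proportional-odds logistic regression, report the common odds ratio with its confidence interval, and check the proportional-odds assumption.
- Show the full grade table by cohort, because ordered tests detect a non-monotone change less well.
- Leave the any-grade 90-day complication rate as the binary primary endpoint, and do not apply the rank-test rule to Clavien–Dindo grades.

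The cost is a sentence or two, with no new data or patients, and the methods are available in the SPSS software the article names. The wording should be settled before data lock, so that the test is not chosen with results in view.

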### Sample size calculation

The sample size calculation is based on safety with non-inferiority for the primary endpoint, the overall 90-day morbidity. In the Dutch national colon cancer audit, the overall postoperative complication rate after MIRH was 26% [22]. As all contributing hospitals within this study are represented in the national database, it can be assumed that the control cohort of the Right study has the same percentage of postoperative complications, i.e. 26%. A non-inferiority margin of 7% was defined. Therefore, introducing the new standardised technique will still be considered safe if the overall postoperative complication rate does not exceed 33%. A total of 1095 patients (365 patient in each of the three prospective cohorts) will be needed to show that there is no difference between the control and experimental (i.e. standardised surgical technique) treatment. With this number of included patients, it can be demonstrated with 80% certainty that the lower limit of the one-sided 95% confidence interval (or equivalently a 90% two-sided confidence interval) will be above the non-inferiority limit of 7%.

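### The statistical analysis section does not carry over the non-inferiority criterion: the between-group test it states for dichotomous outcomes is a chi-square at p < 0.05, which contains no margin

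*Protocol article*

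**What the plan says.** The Sample size calculation section of the protocol article sets the design:

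- Hypothesis: "The sample size calculation is based on safety with non-inferiority for the primary endpoint, the overall 90-day morbidity".
- Control rate: in the national audit, "the overall postoperative complication rate after MIRH was 26" per cent.
- Margin: "A non-inferiority margin of 7% was defined", so the technique "will still be considered safe if the overall postoperative complication rate does not exceed 33" per cent.
- Criterion, with 80% power: "the lower limit of the one-sided 95% confidence interval (or equivalently a 90% two-sided confidence interval) will be above the non-inferiority limit of 7" per cent.
- Size: 1095 patients, 365 in each of three cohorts. The section does not say which cohorts enter the comparison. It describes the patients as needed to demonstrate absence of a difference between the control and the standardised technique.

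The Statistical analysis section has no paragraph on the primary endpoint. For yes/no outcomes it states: "The chi-square test will be used to compare dichotomous and categorical data among patient groups". It also names logistic regression for independent associations, and one threshold: a p "value of less than 0.05 will be considered to be statistically significant". It mentions neither the margin, nor a risk difference with a confidence interval, nor the one-sided 5% level. It defers some decisions to a statistical analysis plan to be completed before data lock. The items listed are stratification, subgroups and baseline imbalance; the primary test is not among them.

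**The concern.** The presence or absence of a 90-day complication is a dichotomous outcome, so by its own wording the chi-square sentence covers the primary endpoint. A chi-square asks whether the data are incompatible with zero difference. Non-inferiority asks whether they exclude an increase of 7 points or more. A non-significant answer to the first question does not answer the second.

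The conclusion at stake is whether the standardised technique was introduced nationally without an unacceptable rise in complications. The sample size text describes the goal as absence of a difference, and the analysis section names a test of difference. Together they leave room for the primary result to be reported as no significant difference when the interval still includes increases above the margin.

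The criterion in the Sample size calculation section is also worded in the wrong direction for a complication rate. With intervention minus control, the upper limit must lie below +7 points. A lower limit above a threshold makes sense only for control minus intervention, and then the threshold is −7 points.

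**Working it through.** **Inputs** (Sample size calculation section): control rate 0.26; margin M = 0.07; one-sided alpha 5% (z = 1.645); power 80% (z = 0.842); 365 per cohort. No dropout is stated, so none is assumed. All figures use the normal approximation unless noted.

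**Step 1. Reproduce the plan's sample size.** With both true rates at 26% and k intervention patients per control,

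n(control) = (1.645 + 0.842)² × 0.26 × 0.74 × (1 + 1/k) / 0.07².

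- k = 2: 6.183 × 0.1924 × 1.5 / 0.0049 = 364.1, so 365 controls and 730 intervention patients, 1095 in total. This matches exactly.
- k = 1: 6.183 × 0.1924 × 2 / 0.0049 = 485.5, so 486 per arm. No match.
- Non-inferiority at one-sided 2.5%: 617 (1:1) or 463 controls (1:2). No match.
- Difference test of 26% vs 33% at two-sided 5%: 666 (1:1) or 504 controls (1:2). At one-sided 5%: 524 or 396. No match.

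Of the variants tried, only the interval criterion with the two intervention cohorts pooled against control gives 365. The design therefore rests on interval versus margin, not on a test of difference.

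Power under that criterion:
- 365 vs 730: SE = √(0.1924/365 + 0.1924/730) = 0.02812; Φ(0.07/0.02812 − 1.645) = 80.1%.
- 365 vs 365: SE = 0.03247; Φ(0.07/0.03247 − 1.645) = 69.5%.

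**Step 2. Chance of a safe conclusion when the true rate is 33%.** Under the interval rule, Φ((0.07 − 0.07)/SE − 1.645) = 5.0% for either comparison.

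If instead a non-significant chi-square at 0.05 were read as safe, the chance is Φ((1.96 × SE₀ − 0.07)/SE₁), with SE₀ pooled and SE₁ unpooled; the other tail is negligible.
- 365 vs 730: pooled rate (0.26 + 2 × 0.33)/3 = 0.3067; SE₀ = 0.02956; SE₁ = 0.02881; Φ((0.05794 − 0.07)/0.02881) = 33.8%.
- 365 vs 365: pooled rate 0.295; SE₀ = 0.03376; SE₁ = 0.03366; Φ((0.06616 − 0.07)/0.03366) = 45.5%.
- One chi-square across the three cohorts (2 df, true rates 26%, 33%, 33%; simulation): about 44%.

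**Step 3. The same contrast on observed data**, with 95/365 control events (26.0%) and 730 pooled intervention patients:

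| Rule | Largest event count accepted | Difference | Upper limit of 90% CI |
|---|---|---|---|
| 90% CI upper limit below 7 points | 207/730 (28.4%) | 2.3 points | 7.0 points (6.998) |
| Chi-square not significant at 0.05 | 231/730 (31.6%) | 5.6 points | 10.3 points |

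Any result from 208 to 231 events fails non-inferiority yet shows no significant difference.

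**Step 4. The opposite error.** With the same control count, the first significant increase is 232/730 (5.75 points, upper limit 10.5) or, for 365 vs 365, 120/365 (6.85 points, upper limit 12.4). Both also fail the 7-point rule.

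**The case against.** The best defence is that the protocol does give the right kind of criterion. The Sample size calculation section names the primary endpoint, the margin and a confidence interval to be compared with it. The chi-square sentence is general: it follows a description of baseline, procedure and perioperative variables and does not name the primary endpoint. A specific criterion should take precedence over a generic one. The analysis plan is still to be completed, and the choice of estimator, interval method and adjustment properly belongs there.

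Much of this stands. A reader might infer that the trial will be judged by a non-significant superiority test. No section says so, and the percentages in Step 2 describe a possible misreading, not a stated rule. It would also be wrong to say that chi-square is the only method named, because logistic regression is named too, although for associations and not against a margin. A reader might further infer that chi-square could condemn a technique lying inside the margin. Step 4 shows that this does not happen at the design rates.

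The defence does not remove the mismatch. The interval sentence is a statement about power, not an analysis instruction, and its direction is muddled. The analysis section does not leave the method open: it states a test and a threshold that do not fit the design, and nothing exempts the primary endpoint. The topics it defers do not include the primary test.

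**Conclusion.** The point holds as a mismatch between design and stated analysis. The trial is designed on an interval-versus-margin criterion, and the analysis section states a margin-free test without linking back to that criterion. The documents do not show that the investigators will equate non-significance with safety.

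If that reading were adopted, the chance of calling a technique safe at a true 33% would rise from 5% to about 34% (365 vs 730) or 45% (365 vs 365). This assumes a true control rate of 26%, no dropout, an unadjusted comparison and a chi-square at 0.05 against zero difference. Which figure applies depends on which cohorts are compared. The protocol does not say, although its own sample size reproduces only as control against the pooled intervention cohorts.

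**What to change.** Settle the following before data lock, in the protocol and the analysis plan:

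1. State the primary analysis as the risk difference in overall 90-day complications, intervention minus control, with a two-sided 90% confidence interval. Non-inferiority is concluded if the upper limit lies below +7 points (one-sided alpha 5%). The interval method, for example Miettinen–Nurminen or a model-standardised difference if adjusted, can be left to the analysis plan.
2. Name the cohorts compared. Control against the two pooled intervention cohorts matches the 365 per cohort. A single 365 vs 365 comparison has 69.5% power, so if that is intended the power statement needs revision.
3. Correct the sentence that asks for a lower limit above the margin, and replace the absence-of-difference phrase with non-inferiority wording.
4. Limit chi-square p-values to baseline and secondary comparisons, and say that a non-significant difference is not evidence of safety.

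The cost is a few sentences and a standard interval calculation. With the pooled comparison, the sample size is unchanged and no new data are needed.

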### Study objectives

The primary objective of this study is to safely implement a standardised technique of MIRH without increasing the 90-day postoperative complication rate, and to ultimately improve long-term outcomes for patients with right-sided colon cancer in the Netherlands. It is hypothesized that this will translate into a reduction of local and distant disease recurrence and thereby an improved 5-year overall survival (OS) and 3-year disease-free survival (DFS).

Secondary objectives are (1) to evaluate current national surgical variations of MIRH and their impact to clinical outcomes (already finished, namely phase 1); (2) to reach consensus concerning the standardised stepwise surgical technique for MIRH using the most recent insights from literature and guidelines and using the Delphi method (already finished) [18]; (3) to design and validate a CAT for the MIRH reflecting all the steps from the Delphi consensus; (4) to evaluate the effect of training and proctoring of the standardised MIRH (comparing control, implementation and consolidation cohorts) on surgical quality and (5) on short- and long-term clinical outcomes.

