Multiple steps of MIRH and their variations can be identified, such as the extent and definition of lymph node dissection (D2 vs D3 lymphadenectomy), and the extent and definition of the CME concept, the type of anastomosis (e.g. intracorporeal or extracorporeal), the extraction site of the specimen (e.g. via a midline incision or via Pfannenstiel) and even smaller details such as use of oral antibiotics and the level of pneumoperitoneum. It is known from the literature that some variations have better clinical outcomes compared to others. The intra- and extracorporeal anastomoses have been extensively studied in MIRH for right-sided colon cancer and an intracorporeal anastomosis provides significantly better short-term outcomes regarding hospital stay, wound infection, time to first flatus and incision length [24–35]. Compared to alternative extraction sites, the Pfannenstiel incision is deemed superior owing to a much lower risk of incisional hernia [36–38]. The extent of the lymphadenectomy within the MIRH for colon cancer is currently a hot topic in the literature, however confusing. Many definitions of CME and D3 lymphadenectomy exist and both terms are incorrectly used as interchangeable concepts [39]. Within the Right study, both CME and D3 lymphadenectomy will be clearly defined within the process of achieving consensus on a standardised MIRH.

The primary outcome of the Right study, 90-day morbidity, was deliberately chosen in order to emphasize the need for a safe and controlled implementation of the optimal standardised technique. This is because any potential oncological benefit might be nullified in case of increased operative risks, which underlines the importance of safety first. If this goal has been achieved, we expect that the implementation and consolidation phases will demonstrate improved long-term oncological outcomes, with decreased recurrence rate and increased survival for patients with right-sided colon cancer in the Netherlands.

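### Kaplan–Meier for locoregional recurrence and distant metastasis, with deaths censored, overstates the absolute risk of two secondary outcomes, probably modestly

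*Protocol article*

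**What the plan says.** The Statistical analysis section gives one rule for this family of outcomes: "Oncological outcomes will be determined using Kaplan–Meier analyses", with groups compared by the log-rank test. It makes no exception and does not mention competing events or cumulative incidence. The regression models it names are logistic and Cox.

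The Outcomes section lists recurrence apart from the survival endpoints: "12) frequency of locoregional recurrence, (13) occurrence of distant metastasis, (14) 3-year DFS, (15) 5-year OS". Neither recurrence outcome is defined as a composite with death.

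The Discussion shows that the authors' term covers recurrence, since it expects "improved long-term oncological outcomes, with decreased recurrence rate and increased survival for patients with right-sided colon cancer". Study objectives makes recurrence the route to benefit: "this will translate into a reduction of local and distant disease recurrence and thereby an improved 5-year overall survival (OS").

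The Statistical analysis section leaves three matters to the later analysis plan: stratification criteria, subgroup analyses and baseline imbalance. Competing events are not among them.

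**The concern.** In DFS and OS death is itself an event, so Kaplan–Meier is suitable. In outcomes 12 and 13 it is not: a patient who dies without the event can no longer have it. Censoring that patient amounts to assuming that the event could still occur at the rate seen in survivors. 1−KM then describes the risk in a hypothetical setting without those deaths, and it is larger than the risk patients actually face. For locoregional recurrence, death after distant metastasis is also a competing event.

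The absolute recurrence risks are what readers would use to judge whether the hypothesised reduction has occurred. The cohorts are sequential and not randomised, so equal competing mortality cannot be taken for granted. If it differs, the actual recurrence risks differ for that reason too, and Kaplan–Meier would not show this.

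**Working it through.** **Inputs.** From the article: the method (Statistical analysis) and the two outcomes (Outcomes). The article gives no rate for recurrence or for death without recurrence, so there is no figure of its own to reproduce on this point. The sample size concerns 90-day morbidity only. The rates below are assumptions, shown over a range.

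**Direction.** Let Λ₁ be the cumulative cause-specific hazard of the recurrence event and Λ₂ that of death without it.

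- 1−KM(T) = ∫ exp(−Λ₁) dΛ₁
- Cumulative incidence CIF(T) = ∫ exp(−Λ₁−Λ₂) dΛ₁

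Since exp(−Λ₂) ≤ 1, 1−KM is never below the CIF, and it is above it once deaths precede some recurrences. This needs no constant hazards.

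**Size.** Take constant, independent hazards r (recurrence) and d (death without recurrence), with T = 5 years.

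- d = −ln(1 − net death risk)/5
- CIF = r/(r+d) × [1 − exp(−5(r+d))]
- 1−KM = 1 − exp(−5r)

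For each assumed true CIF and net death risk, solve for r and then compute 1−KM.

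Worked case, true CIF 15% and net death risk 20%: d = 0.2231/5 = 0.04463. Solving gives r = 0.03650. Check: r/(r+d) = 0.4499; 1 − exp(−0.4056) = 0.3334; product 0.150. Then 1−KM = 1 − exp(−0.1825) = 16.7%, which is 1.7 points or 11.2% relative above the true value.

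| Net 5-year death risk | 1−KM, true 5% | 1−KM, true 15% | Excess, points | Relative excess |
|---|---|---|---|---|
| 5% | 5.1% | 15.4% | 0.1 to 0.4 | 2.5–2.6% |
| 10% | 5.3% | 15.8% | 0.3 to 0.8 | 5.2–5.3% |
| 20% | 5.6% | 16.7% | 0.6 to 1.7 | 11.2–11.5% |
| 30% | 5.9% | 17.7% | 0.9 to 2.7 | 18.2–18.7% |

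The relative excess depends mainly on competing mortality and hardly on the recurrence risk.

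**Between cohorts.** Give two cohorts the same recurrence hazard, with 1−KM = 15% in each: r = −ln(0.85)/5 = 0.03250. Let the net death risk be 20% in one and 10% in the other.

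- 20%: d = 0.04463; CIF = 0.03250/0.07713 × (1 − 0.85×0.80) = 0.4214 × 0.320 = 13.5%
- 10%: d = 0.02107; CIF = 0.03250/0.05358 × (1 − 0.85×0.90) = 0.6067 × 0.235 = 14.3%

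Kaplan–Meier shows 15% in both and hides a 0.8-point difference in actual risk.

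**The case against.** The strongest reply is that the method sentence does not name recurrence. Outcomes 12 and 13 are worded as a *frequency* and an *occurrence* with no time horizon, unlike 3-year DFS and 5-year OS. They could be simple proportions, for which the same section offers "The chi-square test will be used to compare dichotomous and categorical data among patient groups" and logistic regression. That reading is open, and under it this bias does not arise. But the article assigns oncological outcomes to Kaplan–Meier and its Discussion counts recurrence among them, so the time-to-event reading is the better supported one.

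A second reply is that a condensed article may leave competing events to the analysis plan, which is not shown. That plan may well deal with it. Still, the article states a method here and does not merely stay silent, and the point is not among the items it defers.

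A reader might infer more than this, in three ways that the documents do not support:

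- *That the log-rank comparison is invalid.* With deaths censored it validly compares cause-specific hazards of recurrence, as does Cox regression, which the section already names.
- *That Kaplan–Meier contrasts between cohorts would shift with other-cause mortality.* Under constant independent hazards 1−KM depends on r alone. The cumulative incidence is what moves, as the two-cohort example shows.
- *That one figure gives the size.* Assuming only high competing mortality gives a double-digit relative excess. The article supplies no rates, and its exclusion of ASA 4, M1 disease and emergency surgery makes the lower rows of assumed mortality relevant too.

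**Conclusion.** The point holds for absolute risk only. Followed as written, the stated method would overstate the risks of locoregional recurrence and distant metastasis, and it would not display differences in actual risk that come from differing competing mortality. The direction is certain if the two outcomes are analysed as time-to-event, deaths without the event are censored and 1−KM is read as risk. The size rests on assumed rates and constant independent hazards; across the range examined it is probably modest.

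If competing mortality is similar in the three cohorts, all curves are inflated by a similar proportion and the contrast between them changes little. No sample-size or safety conclusion depends on this. It is worth correcting, at minor to moderate weight.

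**What to change.** In the analysis plan, which the article says will be completed before data lock:

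- State that outcomes 12 and 13 are time-to-event outcomes.
- Keep Kaplan–Meier and the log-rank test for DFS and OS.
- For outcomes 12 and 13, estimate absolute risk by the Aalen–Johansen cumulative incidence, with death without that event as the competing event.
- Keep the log-rank or cause-specific Cox comparison for the recurrence hazard, and add a cause-specific Cox model for competing death so that both can be read together. Gray's test or a Fine–Gray model is optional support.

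The cost is wording. No data are needed beyond the recurrence and death dates that the planned analyses already require. SPSS version 23, the named package, may not suffice, so R, Stata or SAS may be needed for these two secondary outcomes.
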